**Methods:**

Overall, 200 participants will be enrolled. Inclusion criteria are patients in the US Department of Veterans Affairs health care system; “severe” COVID-19 infection during the acute phase, defined as requiring hospitalization, within 3-6 months before enrollment; aged ≥18 years; and having 1 of 6 prespecified chronic conditions. All participants will be instructed to use the MouthLab device to capture daily physiological data and complete monthly symptom surveys. Structured data collection tables will be developed to extract the clinical characteristics of those who experience decompensation events (DEs). The performance of the AIDI will depend on the magnitude of difference in physiological signals between those experiencing DEs and those who do not, as well as the time until a DE (ie, the closer to the event, the easier the prediction). Information about demographics, symptoms (Medical Research Council Dyspnea Scale and Post-COVID-19 Functional Status Scale), comorbidities, and other clinical characteristics will be tagged and added to the biomarker data. The resultant predicted probability of decompensation will be translated into the AIDI, where there will be a linear relationship between the risk score and the AIDI. To improve prediction accuracy, data may be stratified based on biological sex, race, ethnicity, or underlying clinical characteristics into subgroups to determine if there are differences in performance and detection lead times. Using appropriate algorithmic techniques, the study expects the model to have a sensitivity of >80% and a positive predicted value of >70%.

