#### Outcome Modeling

We will define the outcome as patients experiencing a DE within τ time units (DEτ). For different values of τ, we will deploy a series of more sophisticated models in order to explore the predictive ability of different approaches, as detailed below. We will split up the data into training and testing datasets based on the time of enrollment. We anticipate an 80:20 split; in other words, we will set aside 20% of the data to evaluate the model performance. For each τ, we will construct a training dataset consisting of multiple overlapping time segments for each patient, which we refer to as the observation period (eg, 2 weeks), and multiple nonoverlapping time segments leading up to the outcome for the patients that experience the outcome, one of which contains the outcome.

Second, we will explore several other machine learning algorithms, including classification trees, random forest, and boosting approaches, to understand whether these more flexible modeling approaches have an advantage over the logistic regression approach. The output of any of these approaches is a predicted probability of a DE occurring within the following τ days given observations of a fixed observation interval (eg, up to 30 previous measurements, or ~2 weeks). As stated earlier, the goal is to develop the AIDI to predict worsening health. The detailed analysis laid out above will allow us to understand the ability of early prediction, that is, the critical time frame just prior to decompensation during which the probability of hospitalization becomes increasingly predictive.

The initial exploratory analysis will inform the selection of proper features for the analysis. We will model the patient’s risk of hospitalization as a function of their physiological values, short-term changes in those values, changes from the baseline, etc. The initial exploratory analysis will inform features such as the appropriate time ranges (eg, should short-term changes be captured since the last reading or over the last 24 hours).

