#### Performance Evaluation

In case of a lower-than-expected number of observed outcomes, or smaller differences than expected between those who experience the outcome and those who do not, we may revert from our 80:20 split to use cross-validation to measure performance. In that case, we will evaluate the algorithm using the leave-one-out cross-validation technique. We will implement this approach by leaving out one patient at a time (corresponding to potentially multiple observation periods to avoid fitting the model on data from the same patient as the model is being evaluated). The leave-one-out cross-validation technique facilitates cross-validation evaluation of the algorithm structure to assess its robustness to changes. This validation step will remake the algorithm for every patient left out of the algorithm development iteration. In short, this approach fits each algorithm using all available data except for (in our case) the data of one patient and then summarizes whether the algorithm predicts the correct classification of decompensation or nondecompensation for each observation period. This process is repeated over all available patients. For each τ, we will summarize the accuracy, false positives, and false negatives.

The resulting predicted probabilities of decompensation will then be translated into the easy-to-communicate AIDI, where there is a linear relationship between the risk score and the AIDI. At the conclusion of phase 3, the final COVID-19 DE detection performance of the AIDI will be evaluated using standard measures including sensitivity, specificity, and positive predictive value across a wide range of risk cutoff values. Overall, AIDI DE detection performance and lead time statistics will be examined across study populations as well as within subgroups. If necessary, to improve prediction accuracy, data may be stratified based on biological sex, race, ethnicity, or underlying clinical characteristics into subgroups to determine if there are differences in performance and detection lead times among the groups.

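### Accuracy by τ is not comparable between horizons, because the share of positive periods rises with τ; compare horizons on measures that do not depend on that share

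*Protocol article*

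**What the plan says.** Under Outcome Modeling, the outcome is a DE within τ, and models are fitted for different values of τ. No values are fixed. For patients with an event, the training data contain "multiple nonoverlapping time segments leading up to the outcome for the patients that experience the outcome, one of which contains the outcome". The same section says this analysis will clarify how early prediction is possible, meaning "the critical time frame just prior to decompensation during which the probability of hospitalization becomes increasingly predictive". The Abstract (Methods) states the pattern that is expected: "the closer to the event, the easier the prediction".

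Under Performance Evaluation, the measures given for each horizon are: "For each τ, we will summarize the accuracy, false positives, and false negatives". The sentence closes the description of leave-one-patient-out cross-validation. For the final AIDI, the same section lists "standard measures including sensitivity, specificity, and positive predictive value across a wide range of risk cutoff values". It also plans lead time statistics and subgroup comparisons. Sample Size sets the operating goal as no false negatives and under 10% false positives.

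**The concern.** A longer window captures more events, so the proportion of positive periods grows with τ whatever the readings contain. Accuracy is a weighted average of sensitivity and specificity, and the weights are the positive and negative shares. Two horizons can therefore differ in accuracy although the index separates cases from controls equally well in both, or not at all.

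The analysis over τ is meant to show how far ahead a DE can be seen. At low alarm rates, accuracy improves as τ shortens with no information in the readings, and that matches the pattern the Abstract expects. Read without a reference value, it could be taken as evidence of a critical time frame.

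The windows are also nested. A period 10 days before a DE is negative at τ = 7 and positive at τ = 14, so both the cases and the controls change with τ.

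**Working it through.** **Inputs from the article.** Event rate 60% with one DE per participant (Sample Size); follow-up of six months (Expected Findings).

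**Assumptions.** τ = 3, 7, 14 and 30 days; six months = 182 days; constant hazard. The article fixes none of these.

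**The plan's own figures.** 100/0.60 = 166.7, against 168 completers stated (168 × 0.60 = 100.8 DEs). 168/0.85 = 197.6, against 200 stated. Both reproduce closely. The article gives no by-τ performance figure to reproduce.

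**Event share.** Hazard = −ln(0.4)/182 = 0.00503 per day, and p(τ) = 1 − exp(−hazard × τ).

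**Accuracy.** Accuracy = Se × p + Sp × (1 − p), so its slope in p is Se − Sp. It is flat in τ only when Se = Sp. An uninformative index that flags a fraction q at random has Se = q and Sp = 1 − q, so the slope is 2q − 1: negative below q = 0.5, zero at 0.5, positive above.

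| | τ = 3 | τ = 7 | τ = 14 | τ = 30 |
|---|---|---|---|---|
| Event share p | 1.5% | 3.5% | 6.8% | 14.0% |
| Accuracy, never alarms (1 − p) | 98.5% | 96.5% | 93.2% | 86.0% |
| Accuracy, 10% random alarms (0.9 − 0.8p) | 88.8% | 87.2% | 84.6% | 78.8% |
| Accuracy, 80% random alarms (0.2 + 0.6p) | 20.9% | 22.1% | 24.1% | 28.4% |
| Accuracy, Se 80% and Sp 90% (0.9 − 0.1p) | 89.9% | 89.7% | 89.3% | 88.6% |
| PPV, Se 80% and Sp 90% | 10.9% | 22.3% | 36.9% | 56.6% |

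PPV = 0.8p/(0.8p + 0.1(1 − p)). For a random index, PPV is simply p. In both cases it falls as τ shortens.

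At τ = 3, the index with 80% sensitivity and 90% specificity has lower accuracy (89.9%) than one that never alarms (98.5%). Accuracy without the all-negative benchmark is therefore hard to read even within one τ.

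**Sensitivity to the model.**
- Events spread evenly over 180 days, p = 0.60 × τ/180: p is 1.0% at 3 days and 10.0% at 30. Never-alarm accuracy is 99.0% and 90.0%; with 10% random alarms it is 89.2% and 82.0%.
- The same model at the 29.8% hospitalization rate cited in Sample Size: never-alarm accuracy is 99.5% and 95.0%.
- Simulation of a random score (200 runs, 168 patients, 60% with one DE, daily prediction times): p is 1.5% and 15.6%, and never-alarm accuracy 98.5% and 84.4%.

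The direction is the same each time; the size depends on how periods are built.

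**Measures free of the event share.** In the simulation, AUC was 0.499 to 0.501 at every τ from 3 to 60 days. With 10% flagged, sensitivity stayed at 0.10 and specificity at 0.90. Error counts moved: false negatives from 2461 at 30 days to 269 at 3, false positives from 1488 to 1918.

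**The case against.** Several points on the other side are sound and limit the claim.

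- **Error rates would expose a useless index.** False positives and false negatives stand beside accuracy for each τ. Read as rates, they are flat in τ for an uninformative index: with 10% random alarms the false-negative rate is 90% at every τ. The under-10% goal in Sample Size is a percentage, which favours this reading. The by-τ sentence does not say which is meant, so this is an ambiguity and not a demonstrated error.
- **The accuracy pattern depends on the cutoff.** The Abstract expects sensitivity above 80%. An uninformative index reaches 80% only by flagging 80% of periods, and its accuracy then falls as τ shortens (28.4% at 30 days, 20.9% at 3).
- **Suitable measures are already planned.** Sensitivity and specificity over many cutoffs are listed for the final AIDI, though not by τ.
- **The link is inferred.** No sentence says that the critical time frame is read from accuracy. Lead time statistics are planned, and the by-τ sentence sits in the account of a fallback method. AUC, intervals and bin widths may also be in an SAP that is not shown.

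A reader might infer more: that accuracy and PPV together make a useless index look better close to the event. That is wrong for PPV, which moves the other way and is not named by τ. A reader might also infer that subgroup differences in PPV will be mistaken for differences in the index. The article plans to "determine if there are differences in performance and detection lead times among the groups" but does not tie that comparison to PPV, and it gives no subgroup event rates.

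What stands is that the by-τ sentence names accuracy, with no event share or benchmark beside it, in an analysis whose stated use is to judge early prediction. That is a choice of measure, not a missing detail.

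**Conclusion.** The point holds in a limited form. Accuracy, and error counts if counts are meant, cannot be compared between values of τ, because the event share rises with τ. Under a 60% rate over 182 days and a constant hazard, the event share alone moves never-alarm accuracy by 12.5 percentage points between 30 days and 3 days (86.0% to 98.5%), and by 10.0 points at 10% random alarms (78.8% to 88.8%). The rise towards short τ holds only below half of periods flagged and reverses above it. The sizes rest on assumed values of τ and on how periods are constructed; that accuracy depends on τ through the event share does not.

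The documents do not show that the study will draw a false conclusion, since rates listed beside accuracy could correct it. This is a cheap improvement, not a flaw that invalidates the analysis.

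**What to change.** Change the by-τ sentence under Performance Evaluation so that:

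1. values of τ are compared on AUC and on sensitivity at a common specificity, for example 90%, in line with the goal of under 10% false positives;
2. false positives and false negatives are stated as rates;
3. accuracy or PPV, where shown for a given τ, appears only beside the event share and the all-negative accuracy (1 − p) for that τ.

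Preferably, read the critical time frame from non-overlapping lead-time bins before the DE (for example 0–2, 3–7, 8–14 and 15–30 days), each set against the same control periods with no DE within the longest τ. This also removes the nesting of windows.

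The cost is a change of wording and a little more programming, with no new data. The downside is wider intervals per bin, since each holds fewer positive periods.

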## Results

Recruitment began in January 2023, and the first patient was enrolled in January 2023. At the time of manuscript submission, 204 patients have been enrolled. Publication of the complete results and data from the study is expected in 2025.

## Discussion

### Expected Findings

The AIDI study seeks to address a substantial challenge, that is, to develop an affordable, scalable, technology-assisted remote monitoring solution to facilitate early identification of abnormalities and timely intervention by clinicians to improve quality of life, functional status, and health outcomes and, ultimately, to reduce the burden of post–COVID-19 condition in the United States and elsewhere. We hypothesize that monitoring participants for 6 months and capturing critical cardiorespiratory parameters on a daily basis in conjunction with subjective and clinical data will enable the development of an index, the AIDI, that will empower high-quality clinical care using the MouthLab device as a rapid and early assessment tool. The outcomes of this research have the potential to redefine the care delivery for COVID-19 and potentially other conditions in the future, as well as push the boundaries of prevention and care beyond traditional care settings into the home.

### Limitations

Self-selection bias may be a limitation of this study as participation is voluntary, and participants already comfortable with using technology might be especially motivated to participate in digital intervention studies. Patients who are particularly ill may not enroll due to difficulty managing the device, and those without cellular service will not be able to participate.

### Strengths

Fully remote study procedures will enhance the accessibility of eligible research participants living in rural or remote locations away from large metropolitan areas. The MouthLab device has built-in SIM cards offering cellular data, thus requiring no other accessory, such as mobile phones, to transmit data to the Aidar Cloud. Using a web application dashboard will allow easier visualization of MouthLab data from all participants, providing us with the opportunity to intervene immediately in the event of absent data or noncompliance.

### Conclusions and Future Work

The findings from this study will result in a predictive algorithm (AIDI) to predict decompensation among high-risk patients who previously had severe COVID-19. In the short term, this could be applied to monitoring such patients during the hospital-to-home transition or for longer periods at home. In the long term, we will adapt and validate the AIDI for monitoring other conditions. Our work will generate insight and guidance for scalable and easy-to-use digital monitoring solutions for remote management of chronic diseases to control disease progression, limiting the impact of comorbidities and, ultimately, improving health outcomes among high-risk populations.

## Abbreviations

AE: adverse event
AIDI: Aidar Decompensation Index
CDW: Corporate Data Warehouse
DE: decompensation event
ED: emergency department
HIPAA: Health Insurance Portability and Accountability Act
ICF: informed consent form
SIM: Subscriber Identity Module
VA: Department of Veteran Affairs
